**Precis**

Increased T cell turnover is one of the main abnormalities observed in HIV infected patients and one of the main mechanisms leading to CD4 lymphopenia. This has led to the hypothesis that medications that act directly to suppress immune activation and normalize T cell turnover, could be used in HIV infection. The purpose of this protocol is to evaluate the effect of the immunomodulatory agent, leflunomide, on CD4+ T cell proliferation in HIV infected adults. HIV infected adults who have stable HIV viral loads and are not taking antiretrovirals will receive leflunomide or placebo for 28 days. CD4+ T cell proliferation will be measured as percent Ki67 expression, and the change in expression from baseline to day 28 will be compared between groups. Various studies measuring immune parameters such as CD4+ and CD8+ T cells counts and level of activation will be collected as well as safety studies and HIV viral loads. The primary study risk is adverse reaction to leflunomide. The study will be double-blinded randomized 2:1 (leflunomide versus placebo) and will be reviewed by a DSMB. Total enrollment for the study will be 18 patients.

Table of Contents

1.0 Background 7

1.1 CD4+ T cell depletion in HIV infection 7

1.2 Immunomodulatory agents in the treatment of HIV infection 7

1.3 De novo pyrimidine synthesis 9

1.4 Leflunomide: metabolism, mechanism of action, and use in rheumatoid arthritis 9

1.5 Leflunomide and HIV *in vitro* 10

1.6 Leflunomide and potential clinical use 11

2.0 Hypothesis 11

3.0 Study Objectives 11

3.1 Primary objective 11

3.2 Secondary objectives 11

4.0 Study Design and Procedures 12

4.1 Design 12

4.2 Endpoints 12

4.2.1 Primary endpoint 12

4.2.2 Secondary endpoints 12

4.3 Sample Size and analysis 12

4.4 Procedures 13

4.4.1 Screening period 13

4.4.2 Treatment period (Day 1 through 28) 14

4.4.3 Post treatment follow up period (Day 29 through 64) 15

**1.0 Background**

## **1.1 CD4+ T cell depletion in HIV infection**

Infection with HIV leads to progressive destruction of CD4+ T cells and clinical immunodeficiency due to CD4+ T cell lymphopenia. There is also a state of increased immune activation that leads to accelerated turnover and death of CD4+ T cells (1,2). Following the initiation of HAART, the rate of turnover decreases but remains abnormally elevated compared to healthy adults despite viral load levels of <50 copies/mL. The direct HIV-mediated killing of CD4+ T cells cannot account for the CD4 lymphopenia observed in AIDS or the inability to restore CD4 counts after viral load suppression to <50 copies/ml. A number of observations have been made that suggest that CD4+ T cell depletion in AIDS is not only related to direct, virus mediated death of infected cells but also to cell death of large numbers of uninfected bystander T cells in the setting of increased activation that follows infection with HIV (1,3).

Several observations have been made that support the theory that chronic immune activation and increased T cell turnover play a central role in the pathogenesis of AIDS. Both CD4+ and CD8+ T cell turnover rates are increased in HIV infected individuals although HIV only infect and directly kills CD4+ T cells (4). Furthermore, CD8+ T cell activation levels can predict the rate of disease progression independent of HIV viral load (5). Level of immune activation prior to seroconversion has also been described to predict faster progression to AIDS (6). Furthermore, the evidence correlating HIV viral load to rate of CD4+ T cell depletion can also be explained if levels of HIV replication correlate with increased level of immune activation and T cell turnover (7-9). Consistent with the idea that HIV-associated CD4+ T cell depletion is not simply the direct result of virus-mediated killing is that SIV-infected sooty mangabeys exhibit only minimally elevated levels of immune activation and do not develop CD4+ T cell depletion despite high levels of virus replication (10).

These observations support the use of immunomodulatory agents in the treatment of HIV infection. Agents such as hydroxyurea and mycophenolate mofetil have been investigated as potential therapeutic agents for HIV infection, however toxicities, risk of infection and lack of clear clinical efficacy have prevented their use in clinical practice.

## **1.2 Immunomodulatory agents in the treatment of HIV infection**

When resting latently infected CD4+ T cells become activated and proliferate, the HIV virus is able to replicate through incorporation with the host cell genome. Therefore, reduction of the number of activated T cells through use of immunomodulatory agents may decrease overall production of the virus. Among the agents that have been evaluated as possible immunomodulating treatment for HIV infection are hydroxyurea, mycophenolate mofetil, steroids, cyclosporine and rapamycin.

Hydroxyurea acts by inhibiting the enzyme ribonucleotide reductase. This inhibition leads to depletion of intracellular deoxynucleotide triphosphates that are necessary for cell division as well as HIV replication. Hydroxyurea leads to cell cycle arrest in G1/S phase and decreases cellular activation. *In vitro* studies on HIV infected lymphocytes have shown that hydroxyurea inhibits viral DNA synthesis (11) and acts synergistically with nucleoside reverse transcriptase inhibitors (12). Clinical studies with hydroxyurea have generally been in combination with didanosine based on the fact that hydroxyurea leads to an increase in the amount of didanosine metabolite and enhanced incorporation into the elongating DNA strand. Though early clinical studies demonstrated that hydroxyurea monotherapy was not effective in decreasing plasma HIV RNA, in combination with didanosine significant reductions in viral load were observed (13,14). Despite these findings, toxicities such as pancreatitis, lactic acidosis and bone marrow suppression have made hydroxyurea an unattractive therapeutic option.

Mycophenolate mofetil inhibits the de novo synthesis of deoxyguanosine triphosphate. Its effects are selective for lymphocytes that depend on de novo synthesis of purines and cannot use salvage pathways for guanosine synthesis. Mycophenolate potentiates the antiviral activity of guanosine inhibitors of reverse transcriptase such as abacavir by depleting the substrate for reverse transcriptase, thus inhibiting HIV replication (15). In addition it induces apoptosis of activated CD4+ T cells, another mechanism by which it may inhibit HIV replication.

Mycophenolic acid has been tested in combination with nucleoside reverse transcriptase inhibitors such as abacavir and didanosine in small pilot studies of patients with multidrug resistant HIV infection (16,17). CD4+ and CD8+ T cell counts remained stable with no change or decrease in plasma HIV RNA. The role of mycophenolate in the treatment of HIV remains unclear and is being studied further.

Corticosteroids have also been studied in HIV infected patients. One uncontrolled study published in 1995 indicated that prolonged administration of corticosteroids resulted in sustained increases in CD4 counts (18). The authors recently published a follow up article in which they retrospectively compared these patients who received prednisolone to a control group matched for baseline CD4+ T cell count and viral load (19). They showed that the prednisolone treated patients had an increase in CD4 + T cell counts of over 200 cells/mm3 in the first two weeks of treatment. On average the counts remained elevated for at least two years. The prednisolone treated patients also showed decreased levels of markers of apoptosis and cell activation as measured by CD25 and HLA-DR expression.

Given the numerous adverse effects of corticosteroids, particularly the increased incidence of avascular necrosis (AVN) of the hip in HIV-infected patients (20), there is heightened concern over the safety of corticosteroid use in the treatment of HIV. A multicenter study of the effects of prednisone on CD4+ T cell count and HIV viral load (ACTG 349) was closed prematurely when information was released about the increased incidence of hip AVN in association with steroids in HIV infected patients (21). In the 24 patients who had been randomized and completed at least 8 weeks therapy, those treated with prednisone experienced a median increase of 45% over baseline in CD4+ T cell count compared to control subjects who had only a 1% increase. The difference, however, did not reach statistical significance. There were also no statistically significant differences in markers of cell activation (HLA-DR and CD38). Furthermore, of 11 patients who volunteered to undergo MRI, two were found to have avascular necrosis. Given these findings, it is not clear what role if any glucocorticoids will play in the treatment of HIV.

## **1.3 De novo pyrimidine synthesis**

Unlike other cells, activated lymphocytes expand their pyrimidine pool by eight to sixteen-fold during proliferation and must use both salvage and de novo pathways of synthesis to meet this demand (22). Pyrimidine synthesis begins with the conversion of glutamine and ATP. Carbamoyl phosphate then condenses with aspartate to form N-carbamoylaspartate which is then converted to the pyrimidine ring dihydroorotate. Dihydroorotate diffuses into the mitochondria where the enzyme dihydroorotate dehydrogenase is located. This enzyme uses quinone as a cofactor to produce orotate which diffuses out of the mitochondria. Orotate is converted into uridine monophosphate (rUMP) in the cytoplasm. Inhibition of de novo rUMP synthesis at the level of dihydroorotate dehydrogenase would lead to decreased levels of rUMP and cells would arrest in the G1 phase of the cell cycle. The metabolite of the immunomodulatory agent leflunomide acts by inhibiting dihydrooratate dehydrogenase and has been shown to cause this effect on activated lymphocytes.

**1.4 Leflunomide: metabolism, mechanism of action, and use in rheumatoid arthritis**

Leflunomide is an isoxazole immunomodulatory agent that was approved by the FDA in 1998 for the treatment of rheumatoid arthritis. Following oral administration, leflunomide is rapidly and almost completely converted to an open-ring metabolite A77 1726, also referred to as M1 (23). The specific site of metabolism is unknown but in vivo and in vitro studies suggest a role for both the GI wall and the liver in drug metabolism. No specific enzyme has been identified as the primary route of metabolism for leflunomide; however, hepatic cytosolic and microsomal cellular fractions have been identified as sites of drug metabolism. M1 has also been identified as an inhibitor of cytochrome P450 isoenzyme 2C9. The primary metabolite, M1, is eliminated by renal excretion as well as by direct biliary excretion and has a half-life of approximately 2 weeks. Because of the long half-life, a drug elimination procedure (cholestyramine 8 g three times daily for 11 days) is recommended to expedite the removal of drug from plasma in the case of unexpected pregnancy or adverse event while receiving leflunomide. Administration of cholestyramine reduces the half-life of leflunomide to one day, most likely by interfering with biliary recycling of M1.

The M1 metabolite is a malononitrilamide to which most of the immunomodulatory effects of leflunomide are attributed. At low therapeutically applicable doses, M1 reversibly inhibits dihydroorotate dehydrogenase (DHODH), the rate limiting step in the de novo synthesis of pyrimidines. This results in inhibition of orotate production and decreased de novo synthesis of rUMP. The diminished level of rUMP results in p53 activation and translocation into the nucleus. After activation of p53, the damaged T cell will arrest in late G1 and not enter the S phase of the cell cycle, required for cell replication (24). As a result, there is inhibition of T cell proliferation resulting in decreased immune response.

The mechanisms of antiproliferative action of leflunomide’s active metabolite are not limited to its effects on pyrimidine synthesis. At higher doses, M1 inhibits tyrosine kinases responsible for early T cell and B cell signaling in the G0/G1 phase of the cell cycle (25). M1 has also been shown to inhibit phosphorylation of the Jak1 and Jak3 tyrosine kinases which are necessary for IL2R signaling (26) and inhibit activation of nuclear factor-B (NF-B) which is critical to the function of cells in the immune system (27).

Leflunomide is used in clinical practice as a disease-modifying antirheumatic drug. It has both anti-inflammatory and immunosuppressive characteristics. It is the first drug to receive the indication of retarding the structural damage of rheumatoid arthritis. The efficacy of leflunomide in the treatment of rheumatoid arthritis was shown in three controlled trials (28, 29). Leflunomide was shown to have significantly superior efficacy as compared to placebo, superior or similar efficacy to sulfasalazine and similar efficacy compared to methotrexate.

## **1.5 Leflunomide and HIV *in vitro***

Because of its unique ability to target and decrease proliferation of activated lymphocytes, leflunomide is an interesting potential therapeutic agent in the treatment of HIV infection. *In vitro* studies have already been completed examining the effect on HIV replication in PBMCs alone and in combination with antiretroviral agents. Its anti-HIV activity has also been studied in comparison to other immunomodulatory agents: hydroxyurea and mycophenolate mofetil.

Hossain et al infected PBMCs with wild-type HIV-1, an NRTI-resistant HIV-1 clone, and a lamivudine-resistant HIV-1 clone and then cultured them in varying amounts of M1, zidovudine and lamivudine (30). The authors found profound inhibition of wild-type HIV-1 infection in as little as 25 uM M1. When tested against the NRTI-resistant HIV-1 clone, M1 enhanced the antiviral effect of zidovudine by more than 20-fold. M1 also significantly inhibited the growth of the lamivudine-resistant HIV-1 clone and contributed to the inhibition of this clone by lamivudine in an additive manner.

Schläpfer et al examined the effect of M1 on HIV replication in PBMCs and tonsillar lymphocytes as compared to hydroxyurea and mycophenolate mofetil (31). All three drugs showed dose-dependent suppression of HIV replication with mycophenolate mofetil showing less potency than M1 or hydroxyurea. Uridine was added before or immediately after HIV infection and was able to restore infection when M1 was given at 25 or 50 umol/L but not at 100 umol/L.

M1 has also been shown to inhibit growth of cytomegalovirus (CMV) and herpes simplex virus (HSV) *in vitro*. Waldman et al have shown that CMV production in both human endothelial cells and fibroblasts is dramatically reduced in a dose-dependent manner over a range of pharmacologically relevant concentrations of M1 (32). It was found to be effective against multiple clinical isolates of CMV including multi-drug resistant isolates. The same group later showed that M1 has similar effects on HSV production in human endothelial cells and Vero cells (33).

## **1.6 Leflunomide and potential clinical use**

Clinical use of leflunomide is not without risks (see below section 9.3.1 Specific Medication Risk). There are potential risks of hepatotoxicity and pancytopenia as well as potential teratogenicity. However, if it is found to be effective in decreasing T cell turnover in HIV infected patients, it may prove useful as an adjuvant therapy in patients receiving non-hepatotoxic or myelosuppressive antiretroviral combinations, as a means of prolonging time to initiation of antiretroviral therapy, or as a means of prolonging interruptions in therapy. Furthermore, analogs of the leflunomide metabolite that have the same mechanism of action but have shorter half-lives and fewer toxicities are under development.

# 2. 0 Hypothesis

At 28 days, HIV-1 infected patients who receive leflunomide 20 mg daily will have lower levels of CD4+ T cell proliferation, as measured by mean percentage of CD4+ cells which express Ki67, compared to HIV-1 infected patients who receive placebo.

# 3.0 Study Objectives

## **3.1 Primary objective**

- To assess the effect of leflunomide on CD4+ T cell proliferation

## **3.2 Secondary objectives**

- To assess the effect of leflunomide on CD8+ T cell proliferation
- To assess the effect of leflunomide on T cell numbers
- To assess the effect of leflunomide on T cell activation
- To assess the effect of leflunomide on spontaneous apoptosis of T cells
- To assess the antiviral effect of leflunomide
- To assess the safety and tolerability of 20 mg of leflunomide for 28 days in HIV-1 infected patients

# 4.0 Study Design and Procedures

## **4.1 Design**

This is a randomized, double-blinded, placebo-controlled study to compare the effect of leflunomide versus placebo on CD4+ T cell proliferation in HIV-1 infected adults following 28 days of treatment. Patients who are determined to be eligible for enrollment will be randomized in a 2:1 ratio to receive leflunomide 20 mg orally, once daily or placebo. The study will consist of a screening period, a 28 day treatment period, and a 29 day post-treatment follow-up period which includes an 11 day drug-elimination period.

## **4.2 Endpoints**

**4.2.1 Primary endpoint**

- Change in % CD4+ cells expressing Ki67

## **4.2.2 Secondary endpoints**

- Change in total number of CD4+ cells expressing Ki67
- Change in total number and % CD8+ cells expressing Ki67
- Change in total and % CD4+ and CD8+ cells
- Change in total and % CD4+ and CD8+ cells expressing HLA-DR and CD38
- Change in total and % CD4+ and CD8+ cells which bind annexin V
- Change in plasma HIV viral load from baseline to end of treatment (baseline = average of H&P and day 1 measurements; End of treatment = day 29 measurement)
- Maximum change in plasma HIV viral load
- Frequency of toxicities and adverse events

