**4.4.3 Post-treatment follow up period (Day 29 through 64)**

On Day 29, the patient’s treatment arm will be unblinded. Patients who were receiving placebo will end study on Day 29. Patients who were receiving leflunomide will begin the drug elimination procedure: cholestyramine 8 grams orally three times a day for 11 days over the following 14 days. On Day 43, a serum A77 1726 level will be measured to assure elimination of the drug metabolite from the serum. Drug level should be less than 0.02 mg/L (or 0.02 ug/mL). If A77 1726 is less than 0.02 mg/L, the patient will end study on Day 64. If the level is above 0.02 mg/L, the 11 day cholestyramine elimination procedure will be repeated, and the study period will be extended as needed.

During the post-treatment follow up period, patients will come in for study visits on Days 29, 43 and 64. On these days, they will have their histories reviewed, urine will be sent for pregnancy testing when appropriate, and blood will be drawn for safety labs, HIV viral load, CD4+ and CD8+ T cell counts. On Days 29 and 43, blood will also be drawn for research studies of lymphocytes including expression of Ki67, expression of activation markers, memory/naïve phenotyping, expression of coreceptors (CCR5 and CXCR4), ELISA for IL-7, TNF level, lymphoproliferative responses, Annexin V staining and *ex vivo* BrdU as well as for measurement of A77 1726. On Days 29 and 43 they will undergo comprehensive physical exams and on Day 64 a targeted physical exam.

Table 1. Procedures

|  | Scr | H&P | D11 | D15 | D29 | D432 | D642 |
| --- | --- | --- | --- | --- | --- | --- | --- |
| Screening consent | X |  |  |  |  |  |  |
| Standard consent |  | X |  |  |  |  |  |
| History | X | X | X | X | X | X | X |
| Comprehensive physical exam |  | X |  |  | X | X |  |
| Targeted physical exam |  |  | X | X |  |  | X |
| EKG and CXR | X |  |  |  |  |  |  |
| HLA testing | X |  |  |  |  |  |  |
| Safety labs3 | X | X | X | X | X | X | X |
| Urine pregnancy test4 | X | X | X | X | X | X | X |
| HIV ELISA5 | X |  |  |  |  |  |  |
| Hep B, C serology6 | X |  |  |  |  |  |  |
| Lipid panel | X |  |  |  |  |  |  |
| HIV viral load | X | X | X | X | X | X | X |
| Flow cytometry | X7 | X7 | X8 | X8 | X8 | X8 | X7 |
| Additional studies9 |  |  | X | X | X | X |  |
| A77 1726 level |  |  | X | X | X | X |  |

1. On Day 1, blood will be drawn prior to administration of study drug

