2. Day 43 and 64 visits will occur only for patients who receive leflunomide
3. CBC with differential, acute care panel, hepatic and mineral panels, amylase, lipase, PT and PTT, urinalysis
4. Serum pregnancy testing can be used if urine is not collected
5. If ELISA positive, proceed with Western blot
6. Hepatitis B surface antigen, hepatitis C antibody, hepatitis C PCR
7. CD4+ and CD8+ T cell counts
8. CD4+ and CD8+ T cell counts, proliferation by intracellular Ki67 expression, expression of activation markers (CD25, CD38, HLA-DR), memory-naïve phenotyping, expression of CCR5 and CXCR4
9. ELISA for IL-7, TNF serum levels, lymphoproliferative responses, Annexin V staining, *ex vivo* BrdU

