**7.0 Adverse Event Reporting**

**7.1 Definitions**

Adverse events (AE): Any unfavorable and unintended diagnosis, symptom, sign (including an abnormal laboratory finding), syndrome or disease which either occurs during the study, having been absent at baseline, or if present at baseline, appears to worsen.

Serious adverse events (SAE): Any untoward medical occurrence that

- 1. results in death
  2. is life-threatening
  3. requires hospitalization or prolongation of existing hospitalization
  4. results in disability/incapacity
  5. results in congenital anomaly/birth defect
  6. other situations such as important medical events (eg. diagnosis of cancer) that may not be immediately life-threatening or result in death or hospitalization but may jeopardize the subject or may require medical or surgical intervention to prevent one of the other outcomes listed above

Unexpected adverse event: An adverse event that is not described in the package insert or current literature with regards to leflunomide or cholestyramine

Relationship assessment: The relationship between a serious adverse event and study drug is determined by the principal investigator. The degree of certainty about causality is graded as follows:

- Unrelated: adverse event is clearly due to extraneous causes
- Unlikely (must have two): adverse event:
  - Does not have temporal relationship to intervention
  - Could readily have been produced by the subject’s clinical state
  - Could have been due to environmental or other interventions
  - Does not follow known pattern of response to intervention
  - Does not appear to worsen with reintroduction of intervention
- Possible (must have 2): adverse event:
  - Has a reasonable temporal relationship to intervention
  - Could not readily have been produced by the subject’s clinical state
  - Could not readily have been due to environmental or other interventions
  - Follows a known pattern of response to intervention
- Probable (must have 3): adverse event
  - Has a reasonable temporal relationship to intervention
  - Could not readily have been produced by the subject’s clinical state or have been due to environmental or other interventions
  - Follow a known pattern of response to intervention
  - Disappears or decreases with reduction in dose or cessation of intervention
- Definite (must have all 4): adverse event
  - Has a reasonable temporal relationship to intervention

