## **7.2 Reporting**

Adverse events: Expected adverse events are those listed in the package inserts for leflunomide and cholestyramine. Adverse events, as well as degree of relationship to study drug, will be entered into a database system; for this system they are graded according to the AIDS Clinical Trial Group (ACTG) Toxicity Table (See Appendix D). For abnormalities NOT found elsewhere on the Toxicity Table they will be assessed for severity:

- Grade 1: Transient or mild discomfort; no limitation in activity; no medical intervention/therapy required.
- Grade 2: Mild to moderate limitation in activity - some assistance may be needed; no or minimal medical intervention/therapy required.
- Grade 3: Marked limitation in activity, some assistance usually required; medical intervention/therapy required, hospitalization possible.
- Grade 4: Extreme limitation in activity, significant assistance required; significant medical intervention/therapy required, hospitalization or hospice care.

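### Adverse event frequency is counted over a study that ends on Day 29 for placebo but Day 64 or later for leflunomide; maximum viral load change shares the problem under some readings

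*Protocol*

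**What the plan says.** Section 4.2.2 names two secondary endpoints without a window: "Frequency of toxicities and adverse events" and "Maximum change in plasma HIV viral load". The viral load endpoint listed just before the second one does have a window: "End of treatment = day 29 measurement".

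Section 7.1 counts as an adverse event any unfavourable sign, laboratory abnormality, "syndrome or disease which either occurs during the study, having been absent at baseline", or any worsening of something already present. The length of the study depends on the arm. Section 4.4.3 says "Patients who were receiving placebo will end study on Day 29", while for leflunomide "If A77 1726 is less than 0.02 mg/L, the patient will end study on Day 64"; if the metabolite has not cleared, elimination is repeated and follow-up is extended. Footnote 2 to Table 1 adds: "Day 43 and 64 visits will occur only for patients who receive leflunomide". Both of those visits include a history, safety laboratory tests and viral load.

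Also under section 4.4.3, treatment is unblinded on Day 29, and leflunomide patients then start 11 days of cholestyramine. Section 7.2 states: "Expected adverse events are those listed in the package inserts for leflunomide and cholestyramine".

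**The concern.** Read together, these sections set a counting period that differs by arm. The leflunomide arm has more days and more laboratory draws in which an event can be found. The added period is also different in kind: assignment is known, and patients take a second drug. Section 9.3.1.2 lists nausea, vomiting, diarrhea, anorexia and abdominal discomfort for cholestyramine. Section 9.3.1.1 lists nausea, vomiting, diarrhea, anorexia and abdominal pain for leflunomide. A whole-study count cannot separate the two drugs by type of event.

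The safety objective in section 3.2 concerns 28 days of leflunomide. At stake is whether the between-arm safety summary answers that question or mixes it with the elimination procedure. A maximum taken over more visits raises a similar issue for viral load.

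**Working it through.** The protocol gives no figure of its own on this point; its sample size calculation (section 4.3) concerns only the Ki67 endpoint.

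**Inputs**
- End of study: Day 29 (placebo) and Day 64 (leflunomide), section 4.4.3.
- Visits after the pre-dose Day 1 draw: Days 15 and 29 in both arms, Days 43 and 64 on leflunomide only (Table 1).
- Patients: 12 leflunomide and 6 placebo (section 4.3).
- Assumed, because the documents give no rate: 28-day risks of 10% to 50%, and a per-draw laboratory toxicity chance of 5% or 10%.

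**Observation time**
- Placebo: 29 − 1 = 28 days. Leflunomide: 64 − 1 = 63 days. Ratio 63/28 = 2.25.
- Post-dose visits: 2 against 4, with 2 of the 4 after the start of cholestyramine.
- Section 4.1 gives a 29-day follow-up period, which would end near Day 57 (28 + 29) and give a ratio of 56/28 = 2.0. Section 4.4.3 and Table 1 both use Day 64, and I follow them. The visit counts do not change.

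**Adverse events, no drug effect, constant rate**

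Risk by Day 64 = 1 − (1 − p)^2.25, where p is the 28-day risk.

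| p | Risk by Day 64 | Expected of 12, Day 64 | Expected of 12, Day 29 | Expected of 6 placebo, Day 29 |
|---|---|---|---|---|
| 10% | 21% | 2.5 | 1.2 | 0.6 |
| 20% | 39% | 4.7 | 2.4 | 1.2 |
| 30% | 55% | 6.6 | 3.6 | 1.8 |
| 50% | 79% | 9.5 | 6.0 | 3.0 |

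The artefact is the step from the fourth column to the third. The difference between 3.6 of 12 and 1.8 of 6 is only the 2:1 allocation. With the ratio of 2.0, the risks would be 19%, 36%, 51% and 75%.

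If a Fisher test were applied, it would falsely reject in 0.4%, 4.6%, 10.8% and 16.4% of trials at these four risks.

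**Laboratory toxicity, chance q per draw**

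1 − (1 − q)^2 against 1 − (1 − q)^4: q = 5% gives 9.8% and 18.5%; q = 10% gives 19% and 34%.

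**Maximum viral load change, no drug effect**

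Simulation of 12 against 6 patients, with independent normal visits of equal SD (assumed). Baseline is the mean of two draws, as section 4.2.2 defines it for the neighbouring endpoint. The test is a two-sided 5% t-test.

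| Meaning of maximum change | Mean, 4 visits | Mean, 2 visits | Rejection, 4 vs 2 | Rejection, 2 vs 2 |
|---|---|---|---|---|
| Largest fall | 1.03 SD | 0.56 SD | about 14% | about 5% |
| Largest absolute change | 1.74 SD | 1.36 SD | about 18% | about 5% |
| Signed change at visit of largest deviation | 0.00 SD | 0.00 SD | 3.7% | about 5% |

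With visit-to-visit (AR1) correlation of 0.3 to 0.5, the first two rejection rates for 4 against 2 visits become 12–13% and 19–20%, so correlation of that size does not remove the effect.

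**The case against.** The strongest reply is that this is an analysis window, which a statistical analysis plan commonly sets. Section 7.1 governs collection and reporting, and those should run to the end of follow-up. Section 7.2 uses the cholestyramine insert only to say which events are expected, which is not a rule for comparing arms. Sections 3.2 and 4.1 frame the trial around 28 days of treatment. Relationship to study drug is recorded, and the arm-specific visits are plain in Table 1, so an analyst would see them.

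Part of this stands. A missing window alone would be no finding. What remains is that the protocol does supply a definition, tied to a study period that it makes longer in one arm. Cutting the count at Day 29 would depart from that definition, and nothing in the document tells the analyst to do so.

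A reader might infer four stronger things that the documents do not support:
- **That a flawed adverse event test is planned.** Section 4.3 leaves secondary endpoints to tests and descriptive statistics as appropriate, and names no adverse event test.
- **That leflunomide will certainly look more toxic.** A higher count is an expectation, and with 6 placebo patients a single trial could show otherwise.
- **That 1.8 of 6 against 6.6 of 12 is the size of the artefact.** Those counts include the 2:1 allocation; the fair contrast is 3.6 against 6.6 of 12.
- **That the viral load endpoint is biased however it is read.** Under the signed reading there is no mean gap and no inflated rejection.

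**Conclusion.** The point holds as a minor flaw in two secondary endpoints. For adverse events, the protocol's definitions give the arms unequal observation (28 against 63 days, 2 against 4 post-dose visits). The additional leflunomide time is open-label and confounded with cholestyramine. Those counts come directly from the text. The size of the distortion does not: it rests on an assumed constant and equal event rate, under which the proportion affected about doubles at the lower risks. That calculation adds nothing for cholestyramine reactions, which could only widen the gap.

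For maximum viral load change, the conclusion is conditional on what the undefined maximum means. The primary Ki67 endpoint and the sample size are not affected. The longer safety follow-up of leflunomide patients is itself right.

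**What to change.** In section 4.2.2, state that between-arm comparisons of adverse event and toxicity frequency, and of maximum viral load change, use first dose through the Day 29 visit in both arms. Define maximum change, for example as the largest fall from baseline. List data after Day 29 separately for the leflunomide arm as elimination-period data, without comparison to placebo.

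A Day 29 cut does not by itself remove all cholestyramine exposure. Under section 6.3, patients who meet a stopping criterion are unblinded, and those on leflunomide start elimination before Day 29; Day 29 data are still sought from them. In patients who stop early, flag events with onset after unblinding or after the start of cholestyramine.

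The cost is wording only. No visit, draw or patient is added or removed, and all Day 43 and Day 64 data are still collected and reported. With equal windows, the simulated rejection rate for maximum viral load change returns to about 5%.
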